## Abstract

**Background:**

Reducing the duration of untreated psychosis (DUP) is an aspiration of international guidelines for first episode psychosis; however, public health initiatives have met with mixed results. Systematic reviews suggest that greater focus on the *sources* of delay within care pathways, (which will vary between healthcare settings) is needed to achieve sustainable reductions in DUP (BJP 198: 256-263; 2011).

**Methods/Design:**

A quasi-experimental trial, comparing a targeted intervention area with a ‘detection as usual’ area in the same city. A proof-of–principle trial, no a priori assumptions are made regarding effect size; key outcome will be an estimate of the potential effect size for a definitive trial. DUP and number of new cases will be collected over an 18-month period in target and control areas and compared; historical data on DUP collected in both areas over the previous three years, will serve as a benchmark. The intervention will focus on reducing two significant DUP component delays within the overall care pathway: delays within the mental health service and help-seeking delay.

**Discussion:**

This pragmatic trial will be the first to target known delays within the care pathway for those with a first episode of psychosis. If successful, this will provide a generalizable methodology that can be implemented in a variety of healthcare contexts with differing sources of delay.

**Trial registration:**

http://www.controlled-trials.com/ISRCTN45058713

## Background

International studies have shown that the average length of time from the onset of psychotic symptoms to first treatment (duration of untreated psychosis; DUP) ranges between 364 and 721 days [1] with recent meta-analyses reporting an association between long DUP and poor outcome at 6 and 12 months, for both symptoms and quality of life. Drake et al. [2] suggest that the point at which DUP *exceeds* three months, defines a critical point after which the likelihood of poorer outcome begins to increase, and several studies indicate that accessing treatment *within* the first 6 months of onset is a key indicator of outcome, specifically in terms of treatment response [3-8].

Evidence for the efficacy of initiatives to reduce DUP, however, is mixed [9]; the ‘TIPS’ study in Norway has had the greatest success. Their prospective trial in a defined health care region, incorporating the introduction of an early detection program alongside a public health awareness campaign, achieved significant results in comparison with parallel health care areas *without* an early detection program. DUP was significantly shorter and associated with better clinical status and reduced suicide risk at baseline and negative symptoms at 12 months, with positive effects on clinical and functional status maintained at 5 year follow-up [10]. However, similar public health initiatives in Australia [11] and Canada [12] have failed to demonstrate any impact on DUP.

Implementation of a TIPS style intervention in UK healthcare settings, however, may prove ineffective as the care pathway delays experienced by young people with first-episode psychosis in UK may not be directly comparable to those experienced in Norway. Rogaland County is a dispersed population centred around the predominantly Caucasian (95%) city of Stavanger [13]; approximately 60% of the population living in urban areas [14]. In contrast, Birmingham, UK is the second most populous city in Britain (1.05m) and the ‘youngest city in Europe’ with 40% of its population under the age of 20. It has a high degree of cultural and religious diversity, including 68% White British residents, 20% residents of Asian or Asian British heritage and 7% Black or Black British, and includes the highest number of residents from the Muslim faith in any UK local area for whom help-seeking can include imams at the family mosque; indeed, our recent study showed that religious construction of psychosis is common [15].

In the UK, the widespread adoption of early intervention in psychosis teams (EIS) have not led to a reduction in DUP [16,17]; this is, perhaps, not surprising since these teams are not resourced or equipped with any *community focused* early detection function. Birmingham, UK, was the setting of the first early intervention service in the UK, yet despite this it continues to experience long DUP [18]. Our cluster randomized trial to improve early detection of psychosis focusing on primary care [16] did not achieve reductions in DUP; further analysis revealed that the main sources of delay occurred elsewhere in the care pathway, in particular, *within* mental health services themselves and in help-seeking delay ^16; 18^. A recent systematic review of interventions to reduce DUP [1] concluded that greater focus on the *sources* of delay within care pathways, (which will vary between healthcare settings) is needed to achieve sustainable reductions in DUP.

Recent data from the UK National EDEN study [19] has confirmed that there are two primary sources of delay: delay in help-seeking among both patients and carers and delays within mental health services. The first referral point to mental health services was found to have the greatest impact on DUP: where the first point of contact was for acute crisis (admission, home treatment), delay within the mental health service was low; where access was via a Community Mental Health Team (CMHT), delays were greatly extended. These findings suggested that whilst improvements in help-seeking behavior are necessary, significant improvements within mental health services themselves would be essential to reduce DUP. In Birmingham, as part of the present study, a youth access pathway into the mental health service has been developed within the CMHT [20], providing a single referral point and ensuring that first episode cases of psychosis are managed in a youth sensitive framework and guarantee direct access to the specialised service.

### Hypothesis

The primary hypothesis to be tested is whether implementation of a psychosis public health campaign *in addition to* the youth access pathway for first episode psychosis, will significantly reduce DUP.

## Methods

### Design

This is a quasi-experimental, proof-of-principle prospective trial comparing an intervention area in the south of the city, to the non-intervention remainder of the city.

Incident cases of first episode psychosis from these areas will be determined and their DUP and care pathways ascertained over the following 18 months. We also benefit from recent historical DUP data (National EDEN) [19] for both target and control areas.

### Sampling

Birmingham is served by a single mental health service, which served as the ‘blueprint’ for the Government’s National Service Framework for Mental Health [21]; it has a number of community services including Home Treatment and Assertive Outreach teams, including well-developed early intervention services for first episode psychosis which were the forerunner of such services across England. It is the second most populous city in Britain with a high degree of cultural and religious diversity and is ranked third most deprived core city in England [22]. Population and ethnic profile of the intervention and control areas [23], together with the number of new cases in the previous 12 months, is shown in Table 1.

**Table 1 T1:** Socio-demographic profile of intervention and control areas

	**Population**	**Ethnic profile**
**Intervention Area**	308,150	85% White British
		8% Asian
		3% Black
**Control Area**	632, 427	62% White British
		26% Asian
		8% Black

### Ethical approval

The trial is sponsored by Research and Innovation department at Birmingham & Solihull Mental Health Foundation Trust. Advice was sought from the National Research Ethics Service for the NHS. This public health trial falls outside of the requirements for formal approval as: no consent or recruitment of service users is required; no identifiable data will be specifically collected or used for evaluation; and the only data to be used will be anonymised DUP data and number of incident cases, both of which are routinely collected for all clients entering the specialist Early Intervention Service (for first episode psychosis) as part of their initial assessment.

### The intervention

#### Context and theoretical framework

The ‘Precede-Proceed’ public health model framework [24] has provided the foundation for this study using assessments of context and setting to inform and guide the development and implementation of the intervention. This will ensure a responsive, stratified ‘knowledge-transfer’ approach is applied to reducing DUP. This framework is further underpinned by two theoretical models of health behaviour change addressing both cognitive *and* contextual determinants; the Trans-theoretical/Stages of Change model [25] and the MINDSPACE framework [26]^,^ the latter arising from behavioural economics, widely employed by UK policymakers [27].

Initial findings from the ‘Precede’ phase of our programme have helped us clarify the likely reasons for delay in care pathways and enabled comprehensive assessment, planning, piloting and target-setting [18]. Patient and public involvement was a fundamental aspect of this preceding phase, involving discussion and consultation with an advisory board comprising of young people and users of the mental health services.

The ‘Proceed’ phase now focuses directly on implementation and evaluation of the intervention, but will, nevertheless, continue to incorporate comprehensive and iterative feedback at each stage to determine the most successful methods of improving help-seeking and youth care pathways.

#### Care pathway interventions

1. Improving help-seeking.

The aim of this component of the intervention is to improve the help-seeking of young people and their carers, who are experiencing symptoms of first-episode psychosis through implementation of a psychosis awareness campaign including information about when, where and how to seek help. Individuals are encouraged to access a helpline and a bespoke website.

The campaign was launched in January 2012 and will run for 18-months. Campaign staff, will be active at the heart of the community, in local shopping centres and supermarkets, at employment centres and community events and will work closely with youth and community groups. All campaign material bears the psychosis campaign slogan, ‘*Don’t turn your back on the symptoms of psychosis’*, the website link (http://www.youthspace.me/psychosis) and the information line number.

The campaign will be broken into 6 three-month stages. Each stage comprising of the following elements:

i. Advertising in high use settings.

Campaign posters will be displayed in a variety of settings, including local bus services and shopping centres. Smaller leaflets and postcards will be routinely distributed across the target areas including supermarkets, employment offices, community and youth groups, leisure centres, coffee shops and fast-food outlets. Informed by our pathfinder studies, the poster themes focus specifically on young people, their friends and parents/carers.

ii. Leaflet drops

Leaflets drops to homes on several large social housing estates in hard-to-reach areas which have no central shopping centre, high street or supermarket.

iii. Advertising in community press

Posters and articles about psychosis, featuring interviews with clinicians and service users, will appear in community newspapers and magazines at regular intervals throughout the campaign; these monthly, bi-monthly and quarterly newspapers and magazines are delivered free to homes in the target areas.

iv. Advertising on community websites

Posters, on-going campaign information and articles about psychosis will be routinely posted on 6 community websites and 10 library web-pages in the target area.

v. Attendance at community events

Campaign volunteers and staff will attend a variety of community and music events and also attend student events at Universities and colleges in the intervention area.

vi. *Promotion of*http://www.youthspace.me/psychosis

Launched in early 2011, our website offers advice, resources, signposting, educational films, blogs and social media access for young people, families/carers and those who work alongside young people on all aspects of mental health and well-being. For the purposes of the psychosis campaign, a direct link to the psychosis specific page of the website will be promoted, providing a variety of information about psychosis, the benefits and importance of early help-seeking, and where to go to seek help.

vii. The Psychosis Information line

A psychosis information line features on all campaign material, offering an alternative way of help seeking for those who would rather *speak* to trained advisors about their concerns or for those who have no access to a computer. A similar line was utilised in the TIPS study. Its main function will be to provide callers with information about psychosis, send out information packs and facilitate access to a clinician for further assessment where appropriate.

viii. Youth Advisors

Youth advisors will regularly update the campaign with photographs, video footage and blogs by those who have experienced mental health issues and ensure we utilise timely and age appropriate creative strategies to engage with young people.

ix. Psychosis Awareness Training

We will collaborate with Emergency Services, youth, community, employment and education agencies to provide psychosis awareness training; this will enable greater outreach into the community and create a broad network of organisations and individuals through which the campaign can be targeted.

2. Youth mental health care pathway.

A youth access care pathway was developed operating alongside existing CMHTs in the intervention area and provides direct referral channels and immediate assessments for all young people presenting to primary care with mental health difficulties aged 14–25 [20]. The service was established to improve the care pathways of young people ensuring that all cases of first episode psychosis have direct access to EIS, enabling and maintaining good levels of engagement with young people from their earliest presentation.

### Inclusion and exclusion criteria

All new cases of first episode psychosis accepted by the Early Intervention in psychosis Service.

Patients considered at ultra-high risk of psychosis, using the Comprehensive Assessment of At Risk Mental State (CAARMS) [28] are excluded. Since this is a pragmatic trial focussing on reducing DUP in patients managed within an EIS, there will be no other exclusions.

### Measures

DUP is routinely calculated for all clients with a first episode of psychosis at entry into EIS services, employing a combination of retrospective assessment of positive and negative symptoms of psychosis (SCI-PANSS) [29], Pathways to Care interview [30] and electronic care records. This is based on the method described by Larsen et al [10] and used in our research [18].

The Pathways to Care interview follows the method of Gater et al. [30] in which systematic information is gathered from direct interview and electronic care records about the source, sequence and timing of help-seeking by patients and their families, including help-seeking contacts, the main problems presented and treatments offered. This included the sequence and duration of contacts within the mental health service. We also documented any mental health service contact prior to the formal onset of psychosis. These data were synthesised onto visual ‘route timelines’; presenting the sequence of help-seeking contacts, referrals made, diagnoses offered, treatment provided and outcomes.

All DUP interviews are conducted by graduate research psychologists, who have satisfactorily completed five DUP calculations, reproducing scores pre-defined by trainers [18]. Each interview takes approximately 1 hour to complete and research staff undergo 6-monthly checks on their assessment reliability, consisting of submission of five timelines and DUP calculations to DUP co-ordinators for concordance and standardisation of calculation. Continual feedback and assistance from co-ordinators was maintained throughout data collection to ensure inter-rater reliability.

### Primary outcome

#### DUP

We hypothesise that our psychosis awareness campaign, *in combination with* the introduction of the youth focused clinical access team, will significantly reduce DUP.

### Secondary outcome

#### Referral rates

We also predict an *increase* in referrals of young people diagnosed with a psychotic disorder from the intervention area into EIS.

Table 2 shows baseline DUP and component delays for incident cases in between August 2011 and August 2012.

**Table 2 T2:** Number of incident cases and their DUP: August 2011 – August 2012

	**New cases**	**DUP (mean; median; sd)**	**Delay in help-seeking (mean; median; sd)**	**Delay within mental health services (mean; median; sd)**	**Delay in accessing EIS (mean; median; sd)**
**Intervention Area**	88	293; 38 (867.1)	50; 0 (131.6)	211; 30 (481.4)	443; 56 (930)
**Control Area**	250	264; 58 (539)	114; 3 (271.4)113	213; 22 (511.9)	323; 105 (560.8)

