### Primary analysis

DUP and referral rates for intervention area compared to the control area will be monitored and evaluated every three months throughout implementation and at the culmination of the intervention (2 year period). In the TIPS study, despite DUP being relatively short in both areas (with a combined median of 10 weeks), DUP was significantly reduced in the intervention area, reduced to a median of 5 weeks compared with 16 weeks in the control area [31]. In this proof-of-principle trial, we make no a priori assumptions about effect size since the methodology and setting is unique. The key outcome of this trial will be an estimate of the effect size, which will inform a definitive trial. The confidence intervals for different levels of increase in the number of new referrals in the target area are shown in Table 3.

**Table 3 T3:** Confidence Intervals for the target area based on predicted increase in referral rate

**Yearly referral rate increase**	***Predicted *****confidence Interval (+/−)**	**CI width**
30	218	90-526
40	187	121-495
50	166	142-474
**60**	**151**	**157-459**
70	139	169-447
80	130	178-438
90	123	185-431
100	116	192-424

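### DUP is summarised over EIS-accepted cases whose number the trial expects to rise, so a change in case mix could move average DUP either way and be mistaken for, or hide, earlier treatment

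*Protocol article*

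**What the plan says.** The Inclusion and exclusion criteria section of the Protocol article takes "All new cases of first episode psychosis accepted by the Early Intervention in psychosis Service", and excludes only patients at ultra-high risk. Under Measures, "DUP is routinely calculated for all clients with a first episode of psychosis at entry into EIS services". The primary hypothesis is that the campaign and youth access team together "will significantly reduce DUP".

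The secondary outcome, Referral rates, predicts an increase "in referrals of young people diagnosed with a psychotic disorder from the intervention area into EIS". The youth care pathway provides "direct referral channels and immediate assessments for all young people presenting to primary care with mental health difficulties" in the intervention area, with the aim of "ensuring that all cases of first episode psychosis have direct access to EIS".

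On analysis, the abstract says that "DUP and number of new cases will be collected over an 18-month period in target and control areas and compared". Primary analysis compares DUP and referral rates between the areas, names an effect-size estimate for a definitive trial as the key product, and adds: "The confidence intervals for different levels of increase in the number of new referrals in the target area are shown in Table 3". The article does not say how the two comparisons are to be read together.

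**The concern.** A patient contributes a DUP value only on entering EIS, and the intervention is meant to change who enters. The set of patients behind the primary outcome is thus itself affected by the intervention, and the predicted rise concerns one area only. Neither the control area nor the historical benchmark removes this, because neither is expected to gain cases in the same way.

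The clearest route is a patient who would have been treated elsewhere and is now routed into EIS. The Background defines DUP as running from symptom onset to first treatment, so if treatment has already begun, that patient's DUP is fixed before EIS entry. The patient joins the average without having been treated any sooner. A second route is outreach: the campaign leaflets hard-to-reach estates and may bring in people untreated for a long time, which raises the average even while the campaign is doing good.

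At stake is the trial's main product. An effect size that mixes earlier treatment with changed case mix could be too large or too small as the basis for planning the definitive trial.

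**Working it through.** **Inputs.** Table 2, intervention area: 88 new cases, mean DUP 293, median 38, SD 867.1 (no unit is printed; days assumed). Table 3: rows from 30 to 100, with 60 in bold. The added cases' DUP is not in the article; 14, 90 and 500 days are assumptions chosen to span short to long.

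**How many cases might be added?** Table 3 heads its rows as a yearly increase. Its intervals do not follow from Table 2. The half-width t(0.975, n-1) × SD / √n with SD 867.1 gives ±224 at n = 60 and ±141 at n = 88 + 60 = 148, against ±151 printed. Every row is centred on 308, for example (157 + 459)/2, and every half-width is reproduced to within 1 day if n equals the row value and the SD is about 584.5. Neither 308 nor 584.5 is in the article; the SD was back-solved from the rows. The rows may therefore be yearly totals, in which case the largest gain over 88 is 100 - 88 = 12. Both readings are carried below.

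**Mean, with the 88 existing cases unchanged.** For k added cases with DUP d:

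mean = (88 × 293 + k × d) / (88 + k), where 88 × 293 = 25,784.

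| Added cases k | d = 14 | d = 90 | d = 500 |
|---|---|---|---|
| 12 | 259.5 (-11%) | 268.6 (-8%) | 317.8 (+8%) |
| 30 | 222.1 (-24%) | 241.4 (-18%) | 345.6 (+18%) |
| 60 | 179.9 (-39%) | 210.7 (-28%) | 376.9 (+29%) |
| 100 | 144.6 (-51%) | 185.0 (-37%) | 403.1 (+38%) |

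For k = 60 and d = 14: (25,784 + 840)/148 = 179.9. For k = 12 and d = 14: (25,784 + 168)/100 = 259.5. The mean is unmoved only if the added cases also average 293.

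**Median.** Without any distributional assumption, k added cases can place the new median anywhere between the [0.5(88 + k) - k]/88 and 0.5(88 + k)/88 quantiles of the existing cases. For k = 60 these are 14/88 = 0.16 and 74/88 = 0.84; for k = 12 they are 38/88 = 0.43 and 50/88 = 0.57. The median is therefore not protected. The two summaries can also move apart: cases added at 90 days lie above the median of 38 and below the mean of 293, so they raise the first and lower the second.

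The quantiles are not converted to days here. A lognormal fitted to the mean and median has σ = √(2 ln(293/38)) = 2.02 and implies an SD of 293 × √((293/38)² - 1) ≈ 2,240, far from the 867.1 in Table 2.

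**The case against.** **The direction is unknown.** A reader might infer that success on referrals would by itself manufacture success on DUP, because wider assessment picks up brief or borderline psychosis. The article does not support that. Nothing in it says that added cases have short DUP, ultra-high-risk patients are excluded, and the predicted rise is in people diagnosed with a psychotic disorder. Outreach could equally find long-untreated cases. This objection stands: the bias is two-directional.

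**Some added cases really are treated sooner.** A person found early by the campaign who would otherwise have come late is the intended effect, not an artefact. This stands too. The problem is confined to people who would otherwise have been treated outside EIS or never have reached it, and the plan gives no way to tell the groups apart.

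**The illustration is soft.** If Table 3's rows are totals, the shift is nearer 11% than 39%. Table 2 also runs from August 2011 to August 2012, across the January 2012 launch, so its 88 cases are not a clean pre-campaign group. Both points limit the size; neither removes the mechanism.

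**This is a condensed article.** Case-mix sensitivity analyses may sit in an analysis plan that is not shown, referral rates are already evaluated beside DUP, and the Pathways to Care interview collects what a case-mix check needs. That is fair, and the point is not that a sensitivity analysis is missing. The article itself fixes the case population, both outcomes and the comparison. Referral rates would show that numbers had changed, but would not say what the change did to DUP.

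**Conclusion.** The point holds in two-directional form. DUP is summarised over a group whose size is predicted to change in one area, and the stated comparisons do not separate that change from earlier treatment. With 60 added cases the mean could move from 293 to anywhere between 180 and 377 under assumed DUPs of 14 to 500 days. With 12 added cases the range is 260 to 318. These figures rest on Table 2 being in days, on existing cases being unchanged, and on the assumed DUP of the added cases. They show what case mix can do, not what it will do.

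The article does not support the stronger conclusion that a fall in DUP would be spurious or that the bias favours the intervention. The change is worth making because the effect-size estimate is the trial's declared key outcome; it does not invalidate the design.

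**What to change.** In Primary analysis, beside the DUP contrast, report new cases per 100,000 residents by DUP band for each area and period: up to 3 months, 3 to 6 months, and over 6 months, the points already cited in the Background. Use the Table 1 populations (308,150 and 632,427) and annualise, since the periods differ in length. For all bands together, Table 2 already gives 88/308,150 = 28.6 and 250/632,427 = 39.5 per 100,000.

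State that the DUP contrast will be interpreted jointly with these rates. A lower average that comes only from added short-DUP cases, with no fall in long-DUP cases, should not be read on its own as earlier treatment. A higher average with more long-DUP cases should not be read on its own as failure. Use the Pathways to Care data already collected to compare referral source between areas and periods.

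Two stronger remedies should be avoided:

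- **Requiring the long-DUP rate to fall before claiming success.** This would penalise a campaign that uncovers hidden long-DUP cases. It would also be imprecise: at roughly 19 such cases a year (a rough figure from the lognormal fit doubted above), comparing one year with 18 months gives a 95% rate-ratio factor of exp(1.96 × √(1/19.2 + 1/28.8)) ≈ 1.8.
- **Lee-type trimming.** It relies on randomised assignment and one-directional selection, neither of which can be assumed in this non-randomised comparison of areas.

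The cost is a little more analysis on data already collected or stated. Band-specific rates will be imprecise because counts are small, so they should be presented with intervals and as description.

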#### UK benchmark DUP data

The trial benefits from extensive DUP data from UK National EDEN sites in Cambridge, Cornwall, Blackburn, Blackpool, Burnley, Lancaster and Norwich [18].

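### Table 2's baseline period, August 2011 to August 2012, includes 6 to 8 months of the campaign launched in January 2012, so its intervention-area row is not a pre-campaign reference

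*Protocol article*

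**What the plan says.** All references are to the protocol article.

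- **Baseline.** Referral rates, under the secondary outcome: "Table 2 shows baseline DUP and component delays for incident cases in between August 2011 and August 2012". The title of Table 2 carries the same dates. The table gives 88 new cases in the intervention area and 250 in the control area, with DUP and component delays for each.
- **Launch.** Care pathway interventions: "The campaign was launched in January 2012 and will run for 18-months".
- **Outcome period.** Abstract: "DUP and number of new cases will be collected over an 18-month period in target and control areas and compared". The Design section has incident cases identified and "their DUP and care pathways ascertained over the following 18 months", without a start date. Under Primary analysis, DUP and referral rates in the two areas "will be monitored and evaluated every three months throughout implementation and at the culmination of the intervention (2 year period").
- **Historical reference.** Abstract: "historical data on DUP collected in both areas over the previous three years, will serve as a benchmark". Design: "We also benefit from recent historical DUP data (National EDEN) [19] for both target and control areas". The section on UK benchmark data lists EDEN sites elsewhere in England.
- **Secondary prediction.** Referrals from the intervention area into the early intervention service (EIS) are expected to rise.

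**The concern.** A baseline should describe the areas before the intervention starts. Here one non-randomised area is compared with the rest of the city, and the two differ at the outset (85% against 62% White British in Table 1). Pre-campaign data are the main means of separating an existing difference from an effect.

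Table 2 cannot do this if much of its window follows the launch. It shows a mean help-seeking delay of 50 days in the intervention area against 114 in the control area, and a median DUP of 38 against 58 days. Help-seeking is what the campaign targets, so a reader cannot tell whether these gaps were there before or are partly early effect.

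Referrals are the most exposed outcome. The three-year historical series is described as DUP data, with no mention of case numbers. The Sampling section says the previous year's new cases are in Table 1, but Table 1 as available here has no such column. The 88 and 250 in Table 2 are therefore the only counts a reader has.

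**Working it through.** The plan gives no figure for the overlap, so there is none to reproduce. The inputs are the dates and counts above. No days of the month are given, so the first and last day of each month serve as bounds.

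**Step 1: overlap.** Share after launch = (window end − launch) / (window end − window start). Expected post-launch cases = share × 88 or share × 250, assuming even accrual.

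| Window | Launch | Days | Months | Share | Of 88 | Of 250 |
|---|---|---|---|---|---|---|
| 1 Aug 2011 – 1 Aug 2012 | 31 Jan | 183/366 | 6.0 | 50% | 44 | 125 |
| 1 Aug 2011 – 1 Aug 2012 | 1 Jan | 213/366 | 7.0 | 58% | 51 | 146 |
| 1 Aug 2011 – 31 Aug 2012 | 1 Jan | 243/396 | 8.0 | 61% | 54 | 153 |
| 31 Aug 2011 – 31 Aug 2012 | 1 Jan | 243/366 | 8.0 | 66% | 58 | 166 |

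The first and last rows are the extremes. If referrals did rise after launch, even accrual understates the post-launch share of the 88.

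**Step 2: the same months as outcome time.** If the 18 months start at launch, the overlap is 6.0/18 = 33% to 8.0/18 = 44% of the outcome window. Evaluation at three-month intervals during implementation makes this the plain reading. No section starts outcome collection after August 2012 or limits Table 2 to pre-launch cases.

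**Step 3: what a before-after contrast would show (illustration only).** Let r be the true yearly referral rate before launch, Δ an immediate and constant increase, and f the share of window time after launch.

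- Baseline rate as tabulated: r + fΔ
- Rate during the campaign: r + Δ
- Apparent change: (r + Δ) − (r + fΔ) = (1 − f)Δ

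With f from 0.50 to 0.66, between 50% and 34% of the change would be visible. The plan does not specify this contrast, and a gradual effect would contaminate less.

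**Step 4: what remains before launch.** The shortest clean stretch, 31 August 2011 to 1 January 2012, is 123 days, or 4.0 months, with 88 − 58 = 30 cases. The longest, 1 August 2011 to 31 January 2012, is 183 days, or 6.0 months, with 88 − 44 = 44 cases.

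**The case against.** The best defence is that little in the plan depends on Table 2. The main comparison is between concurrent areas and needs no baseline. The benchmark that the plan names is the historical series from the preceding three years. No section makes Table 2 a comparator or a covariate, and the control area does not receive the campaign. All of this stands, and it rules out several stronger conclusions that a reader might draw.

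- **That the trial's benchmark is contaminated.** It is not: on its natural reading, the three-year series precedes the trial. Nor does the list of EDEN sites without a Birmingham site overturn the Design section's statement that EDEN data cover both areas. The list may simply describe external sites.
- **That the same cases are certain to be counted twice.** This is an inference. The start of the 18 months is undated, and no section says that Table 2 will enter an outcome contrast. If collection began only after August 2012, double use would disappear but the baseline would still contain campaign months.
- **That a true rise of 60 referrals a year would appear as 25** (60 × 5/12). This assumes an unspecified before-after count analysis, a full effect from 1 January, and a row of Table 3 taken as the true effect.
- **That the bias must run toward no change.** If a campaign first brings in people with long untreated illness, mean DUP could rise in the early months. A baseline that includes those months would then exaggerate a later fall.
- **That Table 3 inherits the problem.** Its intervals are centred on (157 + 459)/2 = 308, not on the Table 2 mean of 293, so it was not built on that row. That mismatch is a separate matter.

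The defence does not remove the date conflict. It also does not supply another count for the referral prediction.

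**Conclusion.** The point holds as a conflict of dates with limited reach. Half to two thirds of the period labelled baseline (6 to 8 months) is campaign time. Under even accrual, about 44 to 58 of the 88 intervention-area cases entered after launch. The overlap in time follows from the stated dates alone, the case numbers rest on the accrual assumption, and the double use rests on the plain reading of the primary analysis section.

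The concurrent comparison of areas and the three-year DUP benchmark are unharmed. What fails is the intervention row of Table 2 as a pre-campaign reference for DUP, component delays and, above all, referrals. Any before-after contrast against it would be biased, by an amount that the documents do not determine. The plan's key product is an effect-size estimate for a definitive trial, so the table should be corrected before it is used for that purpose.

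**What to change.** 1. Define baseline in both areas as cases entering EIS before the January 2012 launch, and give the exact launch date.
2. Re-tabulate Table 2 (DUP, component delays and case counts) for that period. Take DUP from the historical series and counts from the incident numbers that the Ethical approval section describes as routinely collected. Check that component delays are held for the same period.
3. State the start date of the 18-month outcome window and assign each case from launch onward to the intervention period only. Reconcile the 18 months with the two-year period under Primary analysis.
4. State whether baseline must also precede the youth access pathway. The Hypothesis section tests the campaign added to the pathway, while the Primary outcome section tests the two in combination. The documents must reconcile this, because it determines which baseline answers the question.

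The cost is a re-cut of existing data by date and one corrected table. The downside is precision. If only the pre-launch part of the present window is used, about 4 to 6 months and 30 to 44 intervention-area cases remain (even accrual). Using the longer historical series avoids that loss for DUP. For referrals it depends on how far back the routine counts reach, which the article does not say.
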